### Sample size calculation

Sample size is calculated with Sample Power 3. Since there is no data available on MSim or any comparable intervention, the sample size is calculated with an effect size estimation based on results of pilot studies on the chronic effects of WBV on cognition. Two pilot studies used the Stroop test score to evaluate these effects and resulted in an effect size of f = 0.22 [unpublished observations]. Power analyses with this value and use of repeated measures ANOVA, alpha 5%, power 80% and expected drop-out of 15% results in a minimal sample size of 49 participants per group.

Some additional remarks are needed to explain this sample size calculation. Since pilot data for QOL and ADLs are not available, the sample size estimation is based on the secondary outcome measure cognition and not on the primary outcome measures quality of life and daily functioning. Moreover, we are fully aware of the fact that with the calculated sample size additional subgroup analyses lack power. Including these analyses in the sample size calculation would result in unrealistic high sample sizes which would be practically impossible to realize due to factors like available budget, duration of the study and available number of potential participants. Additional analyses will be performed but will be considered exploratory.

### Statistics

For each group, descriptive statistics of the sample’s sociodemographic and clinical characteristics at baseline will be determined. Analyses of covariance (continuous, normally distributed data) or non-parametric alternatives (ordinal, non-normally distributed data) will be used to examine differences between groups at baseline.

Since all primary outcome measures and some of the secondary outcome measures result from questionnaires, they will be of ordinal level of measurement and probably have a skewed distribution. Therefore, non-parametric tests will be used to analyze the data from the questionnaires. Gain scores (post-test minus pretest and follow-up test minus pretest/posttest) will be calculated and the differences between the groups will be analyzed using Kruskall-Wallis tests followed by Bonferoni corrected Mann-Whitney tests for paired comparisons.

The outcome measures related to cognitive and physical function will be of continuous level. If the data satisfy the assumptions, analyses of covariance will be used with scores on cognitive tests at T1/T2 as dependent variables, pretest scores as covariates and group (experimental groups, control group) as between-subjects factor. If the data do not meet the assumptions repeated measures analyses of variance or non-parametric methods with gain scores will be considered. Post-hoc tests will be performed with Bonferoni corrections for multiple comparisons. The data will be analyzed both according to intention-to-treat method (irrespective of adherence to intervention) as per-protocol (for selection of participants with sufficient adherence).

Missing data of items within questionnaires are substituted as prescribed for the individual questionnaires. If no prescription is available, the maximum likelihood method is used to substitute the missing values. Based on the internal consistency of the questionnaires, the maximum number of substituted values will be determined (Cronbach’s alpha >.80, max 50% of the items can be substituted).

A *p*-value of < 0.05 will be used to assess statistical significance. For all tests power and effect size calculations will be performed. Effect sizes will be calculated with Cohen’s d to measure the magnitude of difference of gain score measurements between each experimental and control group. Values benchmarking small, medium and large effect sizes: d = .20, d = .50, d = .80 [48].

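### Primary QOL and ADL scores are compared as raw gain scores with rank tests: valid under randomisation, but less precise than baseline adjustment and an awkward fit with the ordinal rationale

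*Protocol article*

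**What the plan says.** All quotations are from the Statistics section of the protocol article.

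- Of the questionnaire outcomes, which include every primary outcome, it states that "they will be of ordinal level of measurement and probably have a skewed distribution". It concludes: "Therefore, non-parametric tests will be used to analyze the data from the questionnaires".
- The variable to be tested is a difference: "Gain scores (post-test minus pretest and follow-up test minus pretest/posttest) will be calculated".
- The tests are "Kruskall-Wallis tests followed by Bonferoni corrected Mann-Whitney tests for paired comparisons". Neither the baseline score nor any stratification factor enters them.
- For the continuous outcomes the plan differs, on condition that the model assumptions are met: "analyses of covariance will be used with scores on cognitive tests at T1/T2 as dependent variables, pretest scores as covariates". If the assumptions fail, repeated measures ANOVA or non-parametric methods on gain scores are to be considered instead.
- The effect measure is also defined on gains: "Effect sizes will be calculated with Cohen’s d to measure the magnitude of difference of gain score measurements between each experimental and control group".

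**The concern.** Three things do not fit together well.

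1. **Rationale and variable.** The scores are called ordinal, which is one of the two reasons for choosing rank tests. A difference between two ordinal scores can be ranked against another resident's difference only if a step means the same along the whole scale. That is an interval assumption.
2. **Efficiency.** A gain score is a baseline adjustment with the slope set to 1. When the correlation between baseline and follow-up is below 1 and the SDs are similar, the best slope is smaller, so subtraction over-corrects and adds noise.
3. **Estimation.** Cohen's d on gains rests on means and SDs, is not adjusted for baseline, and is not the quantity that the rank tests examine.

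Power and precision on the primary outcomes are at stake. The sample size section concedes that the trial was sized on a secondary outcome (the Stroop test) because no pilot data existed for QOL or ADLs, and that much larger samples were not feasible. Analysis efficiency is one of the few levers that needs no extra residents.

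**Working it through.** **Inputs from the protocol.** Four groups, 1:1:1:1 (Randomization). 49 per group with 15% drop-out (Sample size calculation), so 49 × 0.85 = 41.65, about 42 evaluable. Bounded sum scores, 0 to 120 for the Qualidem and 0 to 90 for the adapted Barthel Index (Outcome measures). Significance level 5%.

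**Inputs assumed.** rho from 0.3 to 0.9, because the protocol gives none for the QOL or ADL scales; equal SD at baseline and follow-up; an illustrative effect of 0.5 SD.

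**The plan's own figure.** With f = 0.22, four groups, 5% and 80%, a one-way ANOVA needs 58 per group, and 58/0.85 rounds up to 69, not 49. The between-group effect of a repeated measures ANOVA, with noncentrality N·f²·m/(1+(m−1)·rho), needs 41 per group at m = 3, rho = 0.55 or at m = 2, rho = 0.40, and 41/0.85 rounds up to 49. So 49 is attainable under plausible but unstated inputs. Those correlations concern the Stroop test and are no evidence about the questionnaires. The present point does not depend on 49 being right.

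**Variance.** With common SD s:

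- gain score: 2s²(1−rho)
- ANCOVA: s²(1−rho²)
- ratio ANCOVA/gain: (1−rho²)/[2(1−rho)] = (1+rho)/2

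The third column is 49 × (1 − ratio). The last two columns use n = 2(1.96+0.84)²·variance/(0.5s)², for two arms, two-sided 5% and 80% power.

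| rho | ratio | equivalent loss of 49 per arm | n per arm, gain | n per arm, ANCOVA |
|---|---|---|---|---|
| 0.3 | 0.65 | 17 | 88 | 58 |
| 0.5 | 0.75 | 12 | 63 | 48 |
| 0.7 | 0.85 | 7 | 38 | 33 |
| 0.8 | 0.90 | 5 | 26 | 23 |
| 0.9 | 0.95 | 2 | 13 | 12 |

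The gain-score variance relative to that of the follow-up score alone is 2(1−rho). Below rho = 0.5, subtracting the baseline is therefore worse than ignoring it.

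**Simulation of the planned rank test.** The formula is normal theory for mean differences, so the four-group test was also simulated: 42 per group, three active arms shifted by 0.5 SD, 1000 runs per setting. The Monte Carlo standard error is at most √(0.25/1000) = 0.016. Power is given as Kruskal-Wallis on gains / ANCOVA / rank ANCOVA:

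| rho | normal data | skewed, bounded 0–120 integers |
|---|---|---|
| 0.3 | 0.43 / 0.68 / 0.65 | 0.38 / 0.64 / 0.65 |
| 0.5 | 0.61 / 0.76 / 0.74 | 0.53 / 0.74 / 0.73 |
| 0.7 | 0.84 / 0.91 / 0.89 | 0.72 / 0.84 / 0.88 |
| 0.8 | 0.95 / 0.97 / 0.95 | 0.89 / 0.95 / 0.97 |
| 0.9 | 1.00 / 1.00 / 1.00 | 0.99 / 1.00 / 1.00 |

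With no effect, rejection rates were 0.035 to 0.058 for Kruskal-Wallis on gains, 0.035 to 0.055 for ANCOVA and 0.033 to 0.058 for rank ANCOVA.

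A second simulation used a skewed 0–90 score with effects of 0.4, 0.4 and 0.5 SD. Kruskal-Wallis on gains reached 48, 59, 73 and 88% power, against 61, 68, 80 and 91% for rank ANCOVA, at rho = 0.5, 0.6, 0.7 and 0.8. The direction is the same, and the gap again narrows as rho rises.

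**The case against.** The case for leaving the plan alone has real force.

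- **No validity problem.** A reader might infer that gain scores bias the comparison through regression to the mean. Under randomisation they do not: chance baseline differences add noise, which the variance ratio already counts, and type I error stays near 5%. This stands.
- **Skewness is a second stated reason for rank tests.** It supports a rank method even if the ordinal argument is dropped, and differencing multi-item totals is ordinary practice. This stands, so the text is awkward rather than self-defeating. Skewness does not, however, call for gain scores.
- **The contrast with cognition is conditional.** A reader might infer that secondary outcomes are assured a better method. ANCOVA is planned there only if its assumptions hold, with gain-score methods among the fallbacks. This stands.
- **The loss may be small.** The same caregiver completes each questionnaire over six weeks (Study procedures), which favours a high rho without fixing it. At 0.9 the loss nearly vanishes. This stands as uncertainty about size.
- **Baseline is used and an effect size is planned.** It would be too strong to say that baseline data are discarded or that only p-values will be reported. Confidence intervals may be left to an analysis plan that is not shown, so their absence is not criticised here.
- **Ceiling effects** limit any analysis of a bounded T1 score, including an adjusted one, and the protocol does not say that residents sit near the ceiling. They are no argument against gain scores in particular.
- **The alternatives have limits too.** Ordinary ANCOVA also assumes interval scaling, and rank ANCOVA gives no difference on the original scale. This stands and shapes the choice of remedy.

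What remains is that the article fixes both the variable and the test, so the point is not detail deferred elsewhere, and that a more precise analysis is available from data the trial already plans to collect.

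**Conclusion.** The point holds as a recommended improvement, not as an error that would undermine the results. The planned test is valid, but it is less efficient than baseline adjustment, and its ordinal rationale does not sit well with subtraction. Elsewhere the protocol itself treats one of these scores as cardinal, by using the EQ-5D-5L index for QALYs (Cost-effectiveness).

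The size depends on a correlation that the protocol does not give. Adjustment is worth 35% of the sample at rho = 0.3, 25% at 0.5, 15% at 0.7 and 5% at 0.9. On skewed, bounded scores with a 0.5 SD effect, the gap in four-group power between the planned test and rank ANCOVA is 0.73 − 0.53 = 0.20 at rho = 0.5, 0.88 − 0.72 = 0.16 at 0.7, and 0.01 at 0.9. These figures rest on equal SDs, about 42 evaluable per arm and assumed effects. The proportional-odds model was not simulated.

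The mismatch between an unadjusted, mean-based Cohen's d and rank tests holds whatever rho is. The documents do not support the stronger inference that the primary comparison is biased or its type I error inflated.

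**What to change.** Analyse each primary score at T1 with its own baseline score as covariate.

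- **Preferred:** a proportional-odds (cumulative logit) model. It respects the ordinal view of the outcome, copes with skewness, and gives an adjusted odds ratio with 95% interval for each intervention against regular care. A three-degree-of-freedom test of group takes the place of Kruskal-Wallis. Baseline can enter as ranks or a spline if linearity is doubted.
- **Alternatives:** rank ANCOVA if only a test is wanted, or ANCOVA with robust standard errors if the authors accept the sum scores as interval. In the latter case the ordinal wording should be amended.
- Keep the Bonferroni correction for pairwise comparisons.
- Keep the gain-score Kruskal-Wallis and Mann-Whitney tests as a sensitivity analysis.
- Make the adjusted odds ratio or difference the main effect measure. Cohen's d on gains can stay as a descriptive supplement.

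The cost is a few sentences in the analysis plan and slightly more programming. Baseline and T1 scores are already scheduled, so visits, recruitment and treatment do not change. The choice should be fixed before outcome data are examined by group.

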**Methods:**

This is a multicenter randomized controlled trial. Three forms of passive exercise are distinguished; motion simulation (MSim), whole body vibration (WBV), and a combination of both MSim + WBV. Intervention effects are compared to a control group receiving regular care. Institutionalized patients with dementia follow a six-week intervention program consisting of four 4–12 min sessions a week.

The primary outcome measures QOL and ADLs and secondary outcome measure care burden are assessed with questionnaires filled in by the primary formal and informal caregivers of the patient. The other secondary outcome measures cognitive and physical functioning are assessed by individual testing. The four groups are compared at baseline, after 6 weeks of intervention, and 2 weeks after the intervention has ended.

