## Methods

### Study design and setting

This is a single blind randomized controlled trial. The study will be conducted in the closed wards of nursing homes in the north of the Netherlands. The effects of three different types of passive exercise will be studied and compared to a control group receiving regular care.

The protocol follows the Standard Protocol Items: Recommendations for Interventions Trials (SPIRIT) 2013 statement [27]. The study protocol is approved by the medical ethics committee of the University Medical Center Groningen (the Netherlands), according to the principles of the Declaration of Helsinki, and is registered with The Netherlands National Trial Register (NTR6290, http://www.trialregister.nl).

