#### Randomization

After baseline measurements and stratification for gender, MMSE score, age and nursing home, participants are randomly assigned (1:1:1:1 allocation ratio) to one of the four groups (MSim, WBV, MSim + WBV or regular care which serves as the control condition) by using random numbers. The randomization procedure is performed by a blinded scientist who is not related to the study.

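### The Bonferroni family for the primary scores is not named; read as all six pairs it is valid but inefficient, and three Holm-tested contrasts against regular care would use the same 5% better

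*Protocol article*

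**What the plan says.** The Statistics section of the protocol article treats all primary outcomes as ordinal questionnaire data. It forms gain scores and compares the groups "using Kruskall-Wallis tests followed by Bonferoni corrected Mann-Whitney tests for paired comparisons". The number of pairs, and so the divisor, is not given. The general threshold is a p-"value of < 0.05 will be used to assess statistical significance". Participants are "randomly assigned (1:1:1:1 allocation ratio) to one of the four groups" (Randomization).

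Elsewhere the comparison of interest is each form against regular care:

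- Abstract, Methods: "Intervention effects are compared to a control group receiving regular care".
- Study design and setting: the three forms "will be studied and compared to a control group receiving regular care".
- Cost-effectiveness: a separate ratio for each form, with regular care as comparator.
- Statistics, last paragraph: Cohen's d on gain scores for each experimental group against control.

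The explicit hypothesis that the combination beats the single forms (end of Background) is worded for cognition, a secondary outcome.

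**The concern.** The family being corrected should match the question being asked. If the correction covers all six pairs, half of the error allowance goes to active-versus-active comparisons on QOL and ADLs, on which no explicit primary hypothesis rests. The three comparisons with regular care are then held to 0.0083 each, with no step-down to recover power once one of them is significant.

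The Sample size calculation section says a substantially larger trial is not feasible. The choice of test family is therefore one of the few ways left to gain power on the primary outcomes. Leaving the family open also means that the threshold could be read as 0.0083 or 0.0167.

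**Working it through.** **Inputs from the protocol article.** Four groups, 1:1:1:1. Alpha 0.05, taken as two-sided (sidedness is not stated). Sample size basis: "alpha 5%, power 80% and expected drop-out of 15" (per cent), 49 per group. Effect size: pilot Stroop data "resulted in an effect size of f = 0.22". For the primary outcomes no figure exists: "Since pilot data for QOL and ADLs are not available". Carrying f = 0.22 over to QOL and ADLs is an assumption, so a range is shown.

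**Analysed per group.** 49 × 0.85 = 41.65, so 41.

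**The plan's own figure.** At f = 0.22 and 80% power, a one-way ANOVA on four groups needs 58 evaluable per group (58/0.85 = 68.2, so 69). The between-group repeated-measures formula with two measurements and correlation 0.4 needs 41 (41/0.85 = 48.2, so 49). At correlation 0.5 it gives 52 with two measurements or 46 with three. The protocol states no correlation, so 49 is attainable but cannot be confirmed.

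**Translating f into d.**
- One group differs from the other three: f = d√3/4, so d = 0.22 × 4/1.732 = 0.508.
- Two against two: f = d/2, so d = 0.44.
- Additive pattern 0, 0.31, 0.31, 0.62: the standard deviation of the means is √(2 × 0.31²/4) = 0.219, again f = 0.22.

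**Thresholds.** Six pairs: 0.05/6 = 0.0083. Three pairs: 0.05/3 = 0.0167. Holm on three: 0.0167, then 0.025, then 0.05. Every p-value below 0.0167 is rejected by Holm, so ungated Holm on three contrasts rejects every control contrast that either reading of the plan would reject.

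**Rough check by hand** (d = 0.508, 41 per group, Mann-Whitney efficiency 3/π). The noncentrality is 0.508 × √(41/2) × √0.955 = 2.25. Power at 0.0083 is Φ(2.25 − 2.64) ≈ 35%; at 0.0167 it is Φ(2.25 − 2.39) ≈ 44%. The difference is about 9 points before any step-down.

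**Simulation** (41 per group, normal data; 10,000 trials per scenario, 8,000 for the additive rows). Mean power per truly active contrast; gains were taken before rounding.

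| Scenario at f = 0.22 | Gate + Bonferroni over 6 | Holm over 3, no gate | Gain (points) |
|---|---|---|---|
| All three active, d = 0.508 | 32.0% | 48.9% | 16.9 |
| One active, d = 0.508 | 31.6% | 41.4% | 9.9 |
| Two active, d = 0.44 | 22.3% | 33.1% | 10.7 |
| Linear gradient | 22.1% | 32.5% | 10.4 |
| Additive, combination arm | 48.9% | 61.5% | 12.6 |
| Additive, single forms | 9% | 19% | 10 |

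With all three active, power for at least one contrast rises from 55.0% to 67.2%.

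**Sensitivity of the gain.**
- 49 per group, f = 0.22: 10.4 to 18.6 points.
- Skewed data, f = 0.22, 41 per group: 10.8 to 17.9.
- d = 0.2, all three active: about 4 to 5. If only one form is active it is somewhat less, about 3.
- d = 0.6: up to 18.6. d = 0.8: 4.7 to 12.4.
- If the correction covered only the three control contrasts (f = 0.22, 41 per group): 2.4 to 9.3.

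**Role of the gate.** Under six pairs, removing only the Kruskal-Wallis gate changes power by about 0.4 points per contrast. Under three pairs the gate costs more: 58.3% against 60.2% with skewed data and one active form.

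**Error under the global null.** Any false claim in the plan's six-pair family: 3.3%. Any false active-versus-control claim: 1.6% to 1.9% for the plan and 3.5% to 4.4% for Holm across the runs. All are within 5%.

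**The case against.** The strongest reply is that nothing here is wrong. An omnibus test followed by corrected pairwise tests is standard and keeps the error rate, and comparing all groups suits a four-group trial. The Abstract says the four groups are compared at each time point. The mechanism paragraph of the Background expects the combination to add to the effects of the single forms without limiting this to cognition. The Discussion says the interventions can be compared with each other. The number of pairs may also be settled in an analysis plan that is not shown.

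Much of this stands. The protocol never states six pairs or 0.0083, and all-pairs testing is a coherent choice. What remains is that the primary comparison as described, and the effect sizes to be reported, are against regular care. Under either reading, Holm on those three contrasts rejects at least as much.

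Stronger readings are tempting but not supported:

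- A reader might infer that gate and Bonferroni together are doubly conservative. Under six pairs the gate costs about 0.4 points; the loss comes from dividing by six without a step-down.
- A reader might infer that the plan wastes more than half of its error allowance. That holds only for the three control contrasts (1.6% to 1.9%); over the family it corrects, the plan uses 3.3%.
- A reader might take one third as the trial's actual pairwise power for QOL and ADLs, or 10 to 17 points as a general gain. Both borrow a Stroop effect size.

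**Conclusion.** The point holds as one of efficiency, not validity. The planned procedure controls error, but the family it corrects is unnamed and, on its natural reading, twice as large as the comparison with regular care requires. The gain from three Holm-tested contrasts is about 10 to 17 points per contrast, given six pairs, 41 analysed per group and f = 0.22. It is about 4 to 19 points across d = 0.2 to 0.8 and 41 to 49 per group, where the lower end assumes that all three forms work. It is about 2 to 9 points at f = 0.22 if three pairs were intended all along. At d = 0.2 power is poor under either procedure.

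The 5% limit applies to one score and one gain score at a time. Neither procedure covers the several primary questionnaires and time points, and the change should not be presented as doing so.

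**What to change.** For each primary QOL and ADL score, name three primary contrasts: MSim, WBV and MSim + WBV, each against regular care. Test them by Mann-Whitney on gain scores with Holm's procedure at 5%, without requiring a significant Kruskal-Wallis test first. Report the three active-versus-active comparisons as secondary. Replace Bonferroni by Holm wherever else post-hoc correction is planned, including the cognitive and physical outcomes; for the same family Holm rejects everything that Bonferroni rejects. Settle this before any outcome data are compared by group.

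The cost is a few lines of text and the loss of confirmatory status for active-versus-active comparisons on QOL and ADLs. If the sponsor wants those comparisons to be confirmatory, the plan should say so and name all six pairs. If only three pairs were intended, the change reduces to stating that, adding the step-down and dropping the gate.
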